### Isometric muscle strength proximal to the cuff

Unilateral isometric muscle strength will be measured at the start and end of the 3 weeks. Measurements will be taken using a wireless digital microFET2 hand-held dynamometer (Hoggan Scientific LLC, Drapper, UT, USA) for hip extension only (see Fig. 4). Isometric hip extension strength will measure muscular adaptations proximal to the cuff. Participants will be tested on a clinical examination couch using procedures often applied in the clinical setting [59]. This test was chosen as isometric loading induces less stress on the musculoskeletal system than eccentric loading (‘break-test’), which is a key consideration when testing individuals with a physical injury [60]. A long lever arm will be utilised during the test to ensure the tester’s strength exceeds the isometric force applied by the participant. The examiner will apply resistance in a fixed position whilst the participant exerts a 5 s isometric maximal voluntary contraction (MVC) against the dynamometer and the examiner. Participants will perform four consecutive attempts with a 30 s recovery between attempts. Strength measures will be reported as Newtons (N). The highest value will be used for analysis purposes. Good interrater reliability (ICC 0.76–0.79) and low test-retest variation (< 10%) has been demonstrated for the HHD measurement technique in measuring isometric muscle strength [59].

**Fig. 4 Fig4:**
[figure not shown]
Hip extension strength measure using microFET-2 hand-held dynamometer (HHD)

### Multi-stage locomotion test (MLFT)

The objective of this test is to assess the participant’s maximal walk/run distance [61, 62]. The test requires the participant to walk/run on a 20 m track at gradually increasing speeds until they are unable to continue due to an increase in symptoms. Speed is controlled by paced-auditory cues accompanied by recorded verbal instructions. The test will be terminated once a patient fails three consecutive attempts at reaching the designated marker at the sound of the audible cue. Total distance covered in metres will be recorded.

### Figure of 8 test

This test measures the participant’s agility and acceleration/deceleration ability on a flat surface. Within the limitations of their injury, each participant will be required to complete 3 laps of a figure of 8 walk/run at maximal speed, in accordance with established guidelines [63].

### Y-balance test

This test developed by Plisky et al., [64] assesses lower-body balance and flexibility using the Y-Balance test kit®. Standing through a single supporting limb on the test kit, the participant will reach with the free limb as far as possible along three lines positioned in anterior, posteromedial and posterolateral directions on each leg (see Fig. 5a–c). The test is currently used as a measure of postural control in patients undergoing UK military lower-limb rehabilitation.

**Fig. 5 Fig5:**
[figure not shown]
Y Balance test: **a** anterior, **b** posteriomedial, **c** posteriolateral reach direction

### Pain perception

It is recognised that BFR training can cause mild muscle discomfort. A visual analogue scale (VAS) will be used to measure pain intensity. The VAS uses a 100 mm horizontal line anchored by the terms ‘no pain’ (0) and ‘worst possible pain’ (100). The VAS response format has shown good internal consistency, is easy to understand, is in wide clinical use, and has been sufficiently evaluated in clinical trials [65]. It is useful in this prospective study of twice daily LI-BFR training sessions to record pain scores in the injured limb. This will be recorded immediately prior to starting the exercise, during the exercise and then 5 min post-exercise. This will be repeated every five BFR training sessions to monitor how pain response changes over time to the BFR intervention.

### Sample size

As this is a pilot-feasibility study we will not perform a formal sample size calculation determined by statistical assumptions and tests. Sample size recommendations for pilot randomised controlled trials will be followed [66] and will aim for a minimum of 12 participants in each study arm providing full data. Given the time constraints for data collection, we intend to recruit 14 participants into each treatment group (i.e. total sample size of 28). We consider this will provide sufficient data to adequately address the aims of this feasibility study and provide useful information on key issues such as recruitment, retention and acceptability of the LI-BFR intervention. This pragmatic preliminary sample will inform a power analysis for a full-scale RCT.

### Statistical analyses

Data generated from this pilot study will help inform a future fully-powered RCT by testing the study procedures. We will not use feasibility trial data to formally test for between-group differences, and the analysis will be of a descriptive nature. Therefore, no statistical analyses will be performed for the pilot data. Descriptive statistics (mean, standard deviation (SD), counts (percentage)) will be used to summarise eligibility, consent, randomisation, adverse events, retention, completion and intervention adherence rates. Description of participant demographic and baseline characteristics will be compared and simple tabulation of this pilot data will be presented. The 95% confidence intervals will be calculated to inform a sample size for a future definitive RCT. All participants will be included in the analysis. This statistical analysis of the pilot data will be exploratory only as our sample size will not allow for a definitive analysis. We will recommend progression to a full study application if minimum criteria are reached in key feasibility aims and objectives. These criteria will include a minimum 80% of target participant recruitment over a 6-month period, and a minimum 80% completion of the LI-BFR intervention and outcome measurement.

### Adverse events

All clinical and research staff will receive a brief detailing the procedures for identifying and reporting safety issues including the use of project adverse events forms. Information on any unexpected adverse events deemed to be related to study participation will be collected and reported to the chief investigator within 24 h of its occurrence. Reporting of safety incidents will be duplicated using existing DMRC clinical health and safety reporting procedures and in accordance with the principles of good clinical practice (GCP). It is not anticipated that there will be any risk to study participants.

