In recent years, research demonstrates that the use of blood flow restriction (BFR) combined with low-load resistance exercise (20–40% 1RM) can enhance the morphology and strength response in human muscle tissue [9]. BFR is typically achieved via a pressurised cuff [10], tourniquet [11] or elastic banding [12]. The external pressure applied to the proximal portion of the upper or lower extremities should be low enough to maintain partial arterial inflow into the muscle, but high enough to occlude venous return from the muscle [13]. During periods of immobilisation, the application of BFR alone has been shown to reduce muscular atrophy [14]. However, to optimise muscular development, BFR must be combined with an exercise stimulus (aerobic conditioning or resistance training), with the greatest muscle strength and morphological responses achieved when BFR is combined with resistance training [2].

When supervised by experienced practitioners, low-intensity BFR (LI-BFR) has been shown to be a safe and effective tool to improve strength and function in athletes [15], the elderly [16, 17] healthy adults [18] and during MSK rehabilitation [19–24]. Additional benefits reported with LI-BFR training, is the potential for increases in muscle hypertrophy and strength in muscles located proximal to the applied pressure (i.e. muscles not direct under BFR) as a result of pre-fatigue of the muscles below the cuff [25]. It is possible that this additional muscle stimulus proximal to the cuff (e.g. in the Gluteus Maximus muscle during a squat or leg press) may further enhance physical function and accelerate progression during MSK rehabilitation. Adverse events to acute sessions of LI-BFR have been reported and primarily include delayed onset of muscle soreness, numbness, fainting/dizziness and bruising [26]. There have also been case study reports of rhabdomyolysis [27, 28] and retinal occlusion [29] in the literature. However, when appropriately supervised, LI-BFR is widely acknowledged as a safe mode of exercise in healthy adults [30].

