**Fig. 1 Fig1:**
[figure not shown]
Lower limbs rehabilitation pathway at DMRC, Headley Court

Of particular interest, in relation to the UK military model of exercise rehabilitation (Fig. 1), is the evidence of muscular hypertrophy and strength demonstrated with high frequency (twice a day) BFR training in as little as 6 days [46] and 12 days [47] of training. The effect of this novel training method is yet to be explored across the UK Defence Medical Services (DMS). Therefore, the purpose of this study is to assess the feasibility of LI-BFR training in a heterogeneous group of lower-limb injured military personnel, under the conditions provided during a 3-week intensive residential rehabilitation centre. This includes measuring the hypertrophic and strength response but also reporting any potential adverse events, monitoring compliance and the pain response over time and whether frequent daily use of this clinical tool is feasible in a busy MDT clinical rehabilitation setting where other potentially conflicting clinical priorities exist. This protocol describes the design and analysis plan for a randomised controlled feasibility study.

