## Methods/design

The primary aim of this study is:To assess the acceptability, feasibility and adverse events associated with implementing a high-frequency LI-BFR intervention in a 3-week intensive residential MDT rehabilitation setting.To assess the feasibility of a future definitive RCT by assessing participant eligibility, monitoring recruitment and retention rates, group allocation acceptance and adherence to the intervention.

The secondary aim is to compare the effects of LI-BFR training against conventional resistance training on cross-sectional area (CSA) and volume of the quadriceps and hamstring muscle groups and muscle strength in UK military personnel undergoing lower-limb injury rehabilitation. Changes in relevant musculoskeletal variables of treatment routinely measured as part of the standard UK military rehabilitation care pathway will also be assessed. This includes walk/run assessment, balance, pain perceptions and compliance to the exercise rehabilitation programme.

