### Primary outcome measure: feasibility and acceptability of LI-BFR intervention

The main focus of this study is feasibility and acceptability for recruitment, retention and measurement of the LI-BFR intervention. Recruitment rates will be measured as the rate of eligible participants invited and consenting into the study. Acceptability of allocation/randomisation procedures will be assessed by examining the reasons for drop-out in any discontinuing participants and by comparing attrition rates between groups. Session adherence rates will be recorded to provide a measure of compliance with the intervention. Strengths, weaknesses and safety of LI-BFR intervention will be assessed by qualitative interviews with the project supervisor, lead exercise rehabilitation instructor, participant feedback and examination of any adverse event reports. We will also aim to provide an estimate of the recommended sample-size for a fully-powered future RCT [55].

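### The only adverse-event collection rule stated is narrower than the primary aim, and can leave the known blood-flow-restriction events out of the planned count

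*Protocol article*

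**What the plan says.** All references are to the protocol article.

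- **Primary aim (Methods/design).** The first aim covers "acceptability, feasibility and adverse events associated with implementing a high-frequency LI-BFR intervention".
- **Purpose (last paragraph of the Background).** The study is to include "reporting any potential adverse events, monitoring compliance and the pain response over time". Nothing here limits events to unexpected or related ones.
- **Primary outcome measure.** Strengths, weaknesses and safety of LI-BFR are to be assessed through interviews with the project supervisor and the lead instructor, and through "participant feedback and examination of any adverse event reports".
- **Statistical analyses.** Adverse events are among the items to be summarised descriptively, with counts and percentages.
- **Adverse events.** The collection rule is: "Information on any unexpected adverse events deemed to be related to study participation will be collected". The same sentence requires such events to reach the chief investigator inside 24 hours. The section also mentions a staff briefing, project adverse-event forms and duplicate reporting of safety incidents through the centre's own procedures. It closes with "It is not anticipated that there will be any risk to study participants".
- **Background.** Events reported after acute LI-BFR sessions "primarily include delayed onset of muscle soreness, numbness, fainting/dizziness and bruising". Case reports of rhabdomyolysis and retinal occlusion are also cited. The same paragraphs describe supervised LI-BFR as safe.

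**The concern.** The aim, the stated purpose and the analysis all concern adverse events in general. The collection rule admits an event only if it passes two filters: unexpected, and deemed related to participation.

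The first filter bears on the events of most interest. Events that the authors list as the main ones reported with this technique are hard to call unexpected. The second filter removes anything judged unrelated, in either arm, although an open comparison of event counts needs no such judgement.

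At stake is the adverse-event table. It is the one quantitative safety summary that the study will hand to the designers of a full trial. If its numerator leaves out the known events, the percentage understates how often participants had them. Events not recorded at the time cannot be reliably recovered later.

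**Working it through.** The plan states no adverse-event rate, so there is no figure to reproduce. The check compares sections, with a short illustration of size.

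**1. Scope of each statement**

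- Aim: adverse events of LI-BFR, without restriction.
- Purpose: any potential adverse event.
- Analysis: adverse events as counts and percentages, without restriction.
- Collection: unexpected **and** deemed related.

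The collection rule is strictly narrower than the other three, and no other section gives a broader rule for recording events.

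**2. What the rule can remove**

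- Soreness, numbness, fainting or dizziness and bruising, if the Background list is taken as showing what is expected. The article has no formal expectedness list, so this step is an inference, though a natural one.
- Any event judged unrelated, in either arm.

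**3. Whether another route restores the count**

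- *Interviews and participant feedback:* may bring events to light, but no rule turns them into participants with an event per arm.
- *Adverse-event reports:* contain whatever the collection rule lets in.
- *Local safety-incident reporting:* may pick up a faint or similar incident, but no count by arm is described.
- *Pain visual analogue scale:* records pain in the injured limb, and its repeated recordings are tied to every fifth BFR session. It does not record numbness, dizziness or bruising, and those recordings have no counterpart in the conventional arm.

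Capture is therefore partial, and none of these routes yields a rate by arm.

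**4. Size, under assumed risks**

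Input from the section Sample size: n = 14 per arm. The true risk p of a named event in the LI-BFR arm is assumed, because the documents give none.

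Expected number affected = n × p. Chance of at least one = 1 − (1 − p)^14.

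- p = 5%: 14 × 0.05 = 0.7; chance 51%
- p = 10%: 14 × 0.10 = 1.4; chance 77%
- p = 20%: 14 × 0.20 = 2.8; chance 96%
- p = 30%: 14 × 0.30 = 4.2; chance 99%
- p = 50%: 14 × 0.50 = 7.0; chance above 99.9%

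On the strictest reading all of these would be filtered out as expected, and 0/14 could be reported. On looser readings the count falls anywhere between 0 and the true number.

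**5. What a genuine zero would mean**

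If 0 of 14 truly had an event, the exact two-sided 95% upper limit is 1 − 0.025^(1/14) = 0.232, or 23%. This limit applies only when all events are recorded. A zero produced by the filter supports no such bound.

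**The case against.** **It may be an expedited-reporting rule.** Unexpected, related and within 24 hours is the usual shape of such a rule, and the briefing, the forms and the local incident route around it are not limited in that way. This is plausible, and it is why the point is not graded higher. But the sentence governs collection as well as reporting, and nothing broader is stated elsewhere.

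**The article is condensed.** What the form records may be set out in the full protocol, which is not shown. That would answer a complaint about missing detail. Here the article states a rule, and that rule conflicts with its own aim, purpose and analysis.

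**No formal comparison of arms is planned.** That is correct: the analysis is descriptive, and the aim concerns LI-BFR. A descriptive percentage is still incomplete if its numerator excludes the known events.

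**Readings that go too far**

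- A reader might infer that a full trial would be recommended because of a falsely low event rate. The documents do not support this. The stated progression criteria are 80% of target recruitment over six months and 80% completion of the intervention and outcome measurement. No adverse-event rate is among them.
- A reader might infer that relatedness will be judged differently in the two arms. Participants and supervising clinical staff are unblinded, so this is possible, but the article does not say who makes the judgement.
- A reader might infer that the known events will go wholly unrecorded. The partial routes above argue against that.

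**Conclusion.** The point holds as an internal conflict. The only stated collection rule is narrower than the primary aim, the stated purpose and the planned summary. Followed as written, it can leave the main known BFR events, and all events judged unrelated, out of the count.

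Under assumed true risks of 10% to 50%, between 1.4 and 7 of 14 LI-BFR participants would be expected to have a named event, against a possible reported count of 0. This range rests on the assumed risks and on treating the Background list as the expected events. It shows what could be lost and is not an estimate of what will be.

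The closing statement on anticipated risk also sits badly with the Background list and with the section Pain perception, which recognises mild muscle discomfort from BFR. That is an inconsistency of wording and affects no analysis.

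Severity: should be fixed. One named component of the primary aim would be answered incompletely, but the sentence may have been meant more narrowly than it reads, some capture exists elsewhere, and no stated progression decision depends on the event rate.

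**What to change.** 1. State that all adverse events are recorded in both arms on the existing form and asked about at the same time points, with expectedness and relatedness as recorded attributes and not as conditions for entry.
2. Add tick-boxes for the events named in the Background.
3. Limit the unexpected-and-related filter to the 24-hour report to the chief investigator.
4. Tabulate participants with at least one event per arm as n/N with exact 95% confidence intervals. This stays descriptive and adds no test.
5. Reconcile the sentence on anticipated risk with the Background and the section Pain perception.

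The cost is a change of wording, a tick-list on a form already in use and slightly more form-filling. The stated event rate will probably look less favourable.

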## Discussion

Optimising the recovery of UK Military personnel suffering MSK injury is of critical importance and has been highlighted as a priority for research by the UK Defence Medical Services. The premise that the use of BFR combined with low-load resistance exercise can enhance the strength response in human muscle tissue may have implications for the rate of recovery in patients undergoing injury rehabilitation. We describe the rationale and design of a feasibility study for the introduction of an LI-BFR intervention into a residential, MDT rehabilitation programme for military patients suffering a variety of lower-limb MSK injuries. To date, this is the first study to establish the preliminary effects of LI-BFR on the muscle volume, strength measures and functional capacity of military personnel undergoing intensive, in-patient rehabilitation. Furthermore, the recruitment methods, safety, intervention adherence and acceptability of a twice daily LI-BFR intervention are essential feasibility components that need to be understood prior to embarking on a fully powered randomised controlled trial. Therefore, the findings from this feasibility study will inform a full-scale trial to determine the effectiveness of LI-BFR during in-patient, MDT rehabilitation. If feasible, military and civilian health care providers could consider LI-BFR as a cost-effective, practical rehabilitation modality to induce muscle adaptation in the absence of high mechanical loading of the lower-limb. The results of the trial will be published when they are available.

## Abbreviations

BFR: Blood flow restriction
CECS: Chronic exertional compartment syndrome
CSA: Cross-sectional area
DMRC: Defence Medical Rehabilitation Centre
DMS: Defence Medical Services
ERI: Exercise Rehabilitation Instructor
GCP: Good clinical practice
LI-BFR: Low intensity blood flow restriction
MDT: Multidisciplinary team
MRI: Magnetic resonance imaging
MSK: Musculoskeletal
MSLT: Multi-stage locomotion test
MVC: Maximal voluntary contraction
PIS: Participant information sheet
RM: Repetition maximum
ROM: Range of motion
ROS: Reactive oxygen species
VAS: Visual analogue scale
